### Plans to give access to the full protocol, participant level-data and statistical code {31c}

The datasets analysed during the current study will be available from the corresponding author upon reasonable request.

## Oversight and monitoring

### Composition of the coordinating centre and trial steering committee {5d}

The World Federation of Chinese Medicine Societies will manage the statistical analysis. The endpoint adjudication committee is the Ethics Committee of Shunyi Hospital of Traditional Chinese Medicine. The Office of Scientific Research in our hospital is the Trial Steering Committee and will supervise the trial, and this group will meet twice per year.

### Composition of the data monitoring committee, its role and reporting structure {21a}

The data monitoring committee (DMC) was established before the study, is independent of the sponsor and has no competing interests. The committee trains researchers on data management. DMC ensures and monitors the quality and completeness of the recorded data.

### Adverse event reporting and harms {22}

All adverse events will be recorded truthfully in the trial. Regarding safety, the patient’s vital signs will be measured, and physical examinations will be performed. The vital sign measurements will include sitting blood pressure, heart rate, respiration rate and body temperature. For acupuncture, the common and expected adverse events include local haematomas, needle breakage, needle retention after treatment, fainting, unbearable prickling, severe pain, persistent discomfort for more than 1 h after acupuncture, local infections and abscesses. The participants will be instructed to report any abnormal reactions or uncomfortable feelings experienced to any researcher. All unexpected recurrent strokes will be recorded in detail in the CRFs, including the time of occurrence, degree of stroke and plausible causes. Participants with mild and moderate stroke (NIHSS score < 22) will be treated for their symptoms and closely monitored as necessary by the researcher. Severe stroke (NIHSS score ≥ 22) will be reported to the research ethics committee, which will provide medical advice to the research team within 48 h, and the research ethics committee will determine whether the trial should be terminated.

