### Participant timeline {13}

All patients will be assessed by a researcher using the above scales on the day of enrolment and 2 weeks, 1 month, 2 months and 3 months after enrolment.

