### Interim analyses {21b}

Descriptive statistics will be used to describe the general status characteristics of patients in detail at baseline, such as gender, age, disease course, and stroke risk factors. Mann-Whitney U test will be used to analyse value changes of FMA, NIHSS, MAS, and BI scores among the groups. Repeated measures analysis of variance (ANOVA) will be used to analyse value changes of FMA, NIHSS, MAS, and BI scores across five testing time points (weeks 0, 2, 4, 8, and 12). Adverse events will be summarised with descriptive statistics.

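### The stated trigger for reporting an on-trial recurrent stroke to the ethics committee is an absolute NIHSS of 22, the upper entry limit, so a large worsening in a mildly affected participant can carry no stated report

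*Protocol article*

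**What the plan says.** The protocol article's section on adverse event reporting and harms {22} sets out what happens when a participant has another stroke. Recording is universal: "All unexpected recurrent strokes will be recorded in detail in the CRFs". Escalation is then split at a single score. Below it: "Participants with mild and moderate stroke (NIHSS score < 22) will be treated for their symptoms and closely monitored as necessary by the researcher". At or above it: "Severe stroke (NIHSS score ≥ 22) will be reported to the research ethics committee". The committee is to advise the team within 48 hours, and "the research ethics committee will determine whether the trial should be terminated".

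The cut refers neither to the participant's score before the event nor to the change from it. The eligibility criteria {10} admit patients with an NIHSS of 5 to 22, so the reporting cut and the upper entry limit are the same number. The secondary outcomes in section {12} describe the NIHSS as running from 0 to 42, with higher scores worse.

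Three other statements bear on the point. Under interim analyses {21b}: "Adverse events will be summarised with descriptive statistics". Under the coordinating centre and steering committee {5d}: "The endpoint adjudication committee is the Ethics Committee of Shunyi Hospital of Traditional Chinese Medicine". The data monitoring committee's stated role {21a} is training in data management and the quality and completeness of the data.

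**The concern.** Everyone in this trial already carries a deficit from the index stroke. A score taken at a recurrence therefore normally contains old and new deficit together, and a fixed total does not measure how much harm the new event did. With the cut at the top of the entry range, the milder a participant was before the event, the more they must worsen before a report is stated.

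What is at stake is oversight. The committee that receives these reports is the one that rules on stopping the trial. Under the printed rule, a severe deterioration in a mildly affected participant has no stated route to it as long as the final score is 21 or lower. The record form and the final descriptive summary keep the information but do not prompt a timely decision.

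**Working it through.** **Inputs**
- Entry range: NIHSS 5 to 22 (eligibility criteria {10}).
- Reporting cut: NIHSS 22 or more (adverse event reporting and harms {22}).
- Scale: 0 to 42 (outcomes {12}).
- Planned sample: 208 (sample size {14}).
- Reading adopted: the NIHSS at the event is the total current deficit. The article does not say so for this rule, but that is how the scale is ordinarily scored.

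The plan gives no derivation of the cut, so there is no figure of its own to reproduce.

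**Formulae.** For a pre-event score *b* of 22 or less:
- rise needed for a stated report = 22 − *b*
- largest rise with no stated report = 21 − *b* (for *b* up to 21)

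| Pre-event NIHSS | Rise needed for a stated report | Largest rise with no stated report |
|---|---|---|
| 5 | 22 − 5 = 17 | 21 − 5 = 16 |
| 10 | 22 − 10 = 12 | 21 − 10 = 11 |
| 15 | 22 − 15 = 7 | 21 − 15 = 6 |
| 20 | 22 − 20 = 2 | 21 − 20 = 1 |
| 21 | 22 − 21 = 1 | 21 − 21 = 0 |
| 22 | 22 − 22 = 0 | none |

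**Recovery before the event.** The pre-event score need not be the entry score. A participant who entered at 15 and improved to 8 needs 22 − 8 = 14 points instead of 7. Recovery below the entry minimum goes further: from 4 the need is 22 − 4 = 18, from 2 it is 20, and from 0 it is 22. So 17 is the largest need only for pre-event scores inside the entry range.

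**The plan's own severity bands.** The subgroup section {20b} uses NIHSS 5–15, 15–20 and 20–22. A move from 5 to 21 crosses from the mildest band to the most severe without reaching the cut.

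**Other stated routes to a timely decision**
- The data monitoring committee's role {21a} does not include safety review.
- The steering committee {5d} meets twice a year.
- The hospital ethics committee is named as endpoint adjudicator {5d}, but recurrent stroke is not among the outcomes in {12}, and nothing says recurrences reach it in that role.

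**Extra reports if every recurrence is reported.** With an assumed recurrence of 1% to 5% over the trial (the document gives no rate): 0.01 × 208 = 2.1 to 0.05 × 208 = 10.4. This is an upper limit, because recurrences at 22 or above are already reported.

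**The case against.** The strongest reply is that this is a condensed article. Expedited and serious-adverse-event procedures commonly sit in the full protocol, which is not shown, and the section never says that strokes below 22 will be withheld from the committee. It describes their clinical handling and names one class that goes up for urgent advice. The cut does harm only if it is the sole route, and the article does not say that it is. This limits the claim to what is stated here. It does not remove the point, because the criticism is of a printed threshold rather than of missing detail: further rules elsewhere could soften the consequence but would not make an absolute 22 suit a population entering at 5 to 22.

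Second, total-deficit scoring is an inference, since the section grades the stroke without saying how residual deficit is treated. That is correct, and every figure above depends on it.

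Third, an absolute cut is simple and identical in both arms, and all recurrences are recorded in detail. Also correct, so no bias between the arms follows.

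Fourth, a change from the last visit can be out of date, because visits are up to a month apart in patients who are recovering. That stands, and is why the report should carry the date of the earlier score.

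A reader might infer more than the documents support in two ways:
- That recurrences below 22 go unreported altogether. They are recorded on the case report forms, and other reporting rules may exist in the full protocol.
- That the rule is faulty at both ends. Near 22 it calls for a report after a rise of 0 to 2 points, which over-reports and errs on the safe side.

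**Conclusion.** The point holds for the low end of the scale. As printed, the rule lets a mildly affected participant worsen by up to 16 points from a score of 5, and by more after recovery below 5, with no report stated in this article to the body that decides on termination. This rests on the NIHSS at the event being the total current deficit and on the routes the article itself states. How many participants would be affected cannot be given, because neither the distribution of entry scores nor a recurrence rate appears in the document.

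This is a weakness in safety oversight that should be corrected. It changes no efficacy estimate, test or between-arm comparison.

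**What to change.** In the section on adverse event reporting and harms {22}, replace the severity split for reporting with one sentence: every on-trial recurrent stroke is reported to the research ethics committee whatever its NIHSS, with the most recent pre-event NIHSS, the date of that score, the NIHSS at the event and the change between them. No new severity cut is needed. The pre-event score is already collected, since the participant timeline {13} schedules the scales at enrolment, 2 weeks, and 1, 2 and 3 months.

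The cost is a short amendment and the few extra reports worked out above. The trial status section expected recruitment to end around February 2022. If follow-up is already complete, the equivalent step is to send the committee all recorded recurrences with the same details.

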### Frequency and plans for auditing trial conduct {23}

The World Federation of Chinese Medicine Societies will manage the statistical analysis. The endpoint adjudication committee is the Ethics Committee of Shunyi Hospital of Traditional Chinese Medicine. The Office of Scientific Research in our hospital is the Trial Steering Committee and will supervise the trial, and the committee will meet twice per year.

### Plans for communicating important protocol amendments to relevant parties (e.g. trial participants, ethical committees) {25}

We will first notify the sponsor and funder of any changes made to the protocol. Then, the PI will notify the centres, and a copy of the revised protocol will be sent to the PI to be added to the investigator site file. We will state all deviations from the previous protocol, which will be fully documented using a breach report form. We will update the protocol in the clinical trial registry.

### Dissemination plans {31a}

The results will be published in a paper after the completion of the study.

## Discussion

According to the results of previous studies [32], acupuncture is beneficial for motor function recovery in stroke patients with hemiplegia and is considered to be safe [33, 34]. The mechanism of motor recovery due to acupuncture in stroke hemiplegia may be related to brain plasticity [35]. Acupuncture in one limb can stimulate bilateral brain areas, increase cerebral blood flow and regulate motor areas damaged by stroke [36]. For example, acupuncture in yanglingquan can regulate multiple brain networks in stroke patients [35]. Thus, it promotes the recovery of hemiplegia limbs.

In this study, ‘hand and foot acupuncture with twelve needles’ includes the acupoints hegu (bilateral), neiguan (bilateral), quchi (bilateral), zusanli (bilateral), yanglingquan (bilateral) and sanyinjiao (bilateral); according to TCM theory (five SHU points of the hands and feet), acupuncture at these points can pass through the meridians, regulating qi and blood.

The FMA can be used to assess motor performance and movement quality in hemiplegic stroke patients [37]. The NIHSS is commonly used to evaluate clinical stroke severity. The MAS is significantly sensitive for assessing changes in the muscle tone of stroke patients with hemiplegia [38]. The BI is highly sensitive to changes in mild stroke patients’ independence performing ADL in the recovery period [39]. Therefore, this study will use the above assessment tools to assess motor function, muscle tension, neurological deficits and patients’ ability to perform ADLs in patients with hemiplegia after stroke.

We present the protocol for a randomised, controlled clinical trial to evaluate the effects of ‘hand and foot acupuncture with twelve needles’. In this study, we will evaluate the effects of different acupuncture treatments on limb dysfunction, limb spasm and patients’ independence in performing ADLs after stroke. The participants will be enrolled for 2 months and followed up for 1 month after the intervention. The data analysts will be blinded to this study design to reduce bias and ensure the quality of this trial. The main limitation of this study is its non-double-blind design. Furthermore, this study will not include data from long-term follow-ups.

### Trial status

This protocol version number is 2.0, dated August 2018. Participant recruitment began on March 8, 2019, and will end on approximately February 28, 2022.

## Abbreviations

DALYs: Disability-adjusted life years
EBM: Evidence-based medicine
TMS: Transcranial magnetic stimulation
ADLs: Activities of daily living
FMA: Fugl-Meyer assessment
BI: Barthel Index
MAS: Modified Ashworth scale
NIHSS: National Institutes of Health stroke scale
ISTCMDS: Ischaemic Stroke TCM Syndrome Diagnostic Scale
PT: Physical therapy
OT: Occupational therapy
STRICTA: Standards for Reporting Interventions in Clinical Trials of Acupuncture
TCM: Traditional Chinese medicine
